#### Social Maturity Scale

The Social Maturity Scale (SMS) was designed to assess a person’s level of development by identifying the actual needs and responsibilities of an individual in daily life. Questions are presented depending on age, and social age is calculated by interpolation of the total score [28]. Higher scores mean a greater degree of social maturity. The assessment will be carried out during the visit at baseline (visit 2), mid-point (visit 14), termination (visit 25), and follow-up (visit 26).

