### Study participants

One hundred twenty children will be recruited from two hospitals (Kyung Hee University Hospital at Gangdong and Kyung Hee University Medical Center, Republic of Korea) through online and offline recruitment notices, including posters and webpages. Those two hospitals have recruited participants in more than 20 clinical trials that eight studies were completed and 19 studies are recruiting in Kyung Hee University Hospital at Gangdong, and 41 studies were completed and 52 studies are recruiting in Kyung Hee University Medical Center. The participants’ guardians will be provided with research information, such as objectives, procedures, and potential benefits and harms, through standardized interviews. Informed consent will be obtained from children’s guardians prior to the screening process. The participants will be allowed to withdraw from the study at any time. The research procedure will be carried out as shown in Figs. 1 and 2. All participants will undergo a 12-week treatment and 12-week follow-up. After the screening session, children will be scheduled for 24 treatment visits (twice a week) and one follow-up visit (12 weeks after last treatment). Guardians will be sent text messages as reminders of the scheduled visits.

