### Random assignment

Subjects who have agreed to participate in this clinical trial are assigned a screening number in the order of their guardian’s written informed consent. After completing the screening test, eligible subjects will be assigned to the UGSJB or placebo group according to their random assignment code. The random assignment codes are provided by an independent statistician in the Korean Medicine Clinical Trial Center (K-CTC), and random sequence numbers were generated by blockrand package 1.3 of R 3.4.2 (2017-09-28). The block random assignment will be made after stratification according to the hospital so that the subjects of each group are approximately identical.

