### Secondary outcome measures

#### Autism Behavior Checklist (ABC^1^)

ABC^1^ was developed by Krug *et al*. for differentiating autistic children from intellectual disability, deaf-blind, emotionally disturbed, or normal children [21]. It provides insight into the general characteristics of what an individual looks like compared with another person. ABC^1^ has a reported internal reliability of 0.87 [22], sensitivity of 0.38–0.58, specificity of 0.76–0.97 [23], and test-retest reliability of 0.83 [24]. A child with a total score above 67 is highly likely to be autistic, and those with a total score between 53 and 67 require further evaluation. The assessment will be carried out during the visit at baseline (visit 2), mid-point (visit 14), termination (visit 25), and follow-up (visit 26).

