### Statistical analysis

Data coding will be kept by the researcher team, and data analysis will be conducted by statisticians who are independent of the research team. Effectiveness data will be analyzed mainly with full analysis set (FAS) and further analyzed with per protocol set (PPS). The FAS is defined as all subjects who have taken at least one prescription in the clinical trial and have at least one measurement of the primary outcome after having the prescription. The PPS is defined as all subjects who have taken more than 118 packs (70% of the total 168 packs). The safety analysis includes all data from the participants who have taken at least one prescription in the clinical trial.

Continuous data will be presented as descriptive statistics such as mean and standard deviation, and any statistical differences between the two groups will be tested by using the independent *t* test or Wilcoxon rank-sum test. Categorical data will be presented as frequency and percentage, and any statistical differences between the two groups will be tested by using the chi-squared test or Fisher’s exact test. If significant differences of baseline are recognized between two groups, analysis of covariance (ANCOVA) or rank ANCOVA will be used. In secondary analyses within groups, continuous data will be analyzed by using the paired *t* test or Wilcoxon signed-rank test, and categorical data will be analyzed by using McNemar’s test.

The significance level is 0.05 for all statistical tests, and two-tailed tests will be performed. Missing values will be imputed by the last-observation-carried-forward method.

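### The only Social Maturity Scale score named is social age, which rises with ordinary development: the within-arm paired tests cannot show a gain in relative maturity, and a between-arm test of visit values loses precision

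*Protocol article*

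**What the plan says.** The SMS stands under "Secondary outcome measures". Its section describes the scoring: "Questions are presented depending on age, and social age is calculated by interpolation of the total score", and then gives the direction: "Higher scores mean a greater degree of social maturity". It does not say whether the total score, the social age or some further derived score enters the analysis. Social age is the only derived score it names.

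The scale is completed four times. Under Study participants, "All participants will undergo a 12-week treatment and 12-week follow-up". The abstract places the assessments at baseline and at 6, 12 and 24 weeks. Children aged 4 to 6 are eligible. Age plays no part in the allocation: "The block random assignment will be made after stratification according to the hospital".

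The Statistical analysis section sets one rule for all continuous data: "any statistical differences between the two groups will be tested by using the independent *t* test or Wilcoxon rank-sum test". ANCOVA or rank ANCOVA comes in only if the groups differ significantly at baseline. The section adds: "In secondary analyses within groups, continuous data will be analyzed by using the paired" t test or the signed-rank test.

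**The concern.** Social age increases as a child grows, treated or not. It also differs between a 4-year-old and a 6-year-old with the same maturity relative to age. Two consequences follow if social age is analysed as described.

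- **Within arms.** The paired test asks whether mean social age is unchanged. For developing children that null hypothesis is false before any treatment effect is considered. A significant gain in either arm then shows that time has passed. Every child also receives acupuncture and there is no untreated arm, so gains in both arms could easily be misread as a benefit.
- **Between arms.** If values at a visit are compared by a plain two-sample test, the age spread sits in the error term. The planned ANCOVA trigger does not reliably recover this. Under valid randomisation, a given baseline variable differs significantly at the 0.05 level in only about 5% of trials. In the rest, the adjustment would not be made on that variable's account.

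**Working it through.** **The plan's own figure.** No figure is given for SMS. The CARS sample size reproduces. Pooled SD = √((5.42² + 5.53²)/2) = 5.475 and difference = 7.9 − 4.6 = 3.3. Noncentral-t power at two-sided 5% is 0.798 for 44 and 0.807 for 45 per group. Then 45/(1 − 0.25) = 60 per group, 120 in total. I use 45 and 60 per arm below.

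**Precision of visit values.** These inputs are assumed and are not in the article: age uniform from 4 to 7 years (mean 5.5, variance 0.75), and social age = q × age, with q independent of age.

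- Variance due to age = mean(q)² × 0.75.
- Remaining variance = SD(q)² × (5.5² + 0.75) = SD(q)² × 31.
- Mean 0.6, SD 0.15: 0.27/(0.27 + 0.6975) = 28%.
- Mean 0.4, SD 0.20: 0.12/(0.12 + 1.24) = 9%.
- Mean 0.8, SD 0.10: 0.48/(0.48 + 0.31) = 61%.

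The sample size needed for equal precision is multiplied by 1/(1 − share): about 1.4 centrally, with a range of 1.1 to 2.5. This model has no measurement error; adding some would lower the shares.

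**Simulation with no treatment effect.** There were 4,000 trials per scenario. Assumed: ages uniform over 48 to 84 months; mean developmental rate 0.3, 0.5 or 1.0 months of social age per calendar month; between-child SD of the rate 0.15; measurement-error SD of change 4 or 8 months.

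Twelve weeks are 12/52.18 × 12 = 2.76 months, and 24 weeks are 5.52 months. Mean growth is rate × time: about 0.8 to 2.8 months at week 12 and 1.7 to 5.5 months at week 24, the same in both arms.

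Percentage of trials in which the within-arm paired t test is significant:

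| Rate | Error SD | n=45, wk 12 | n=45, wk 24 | n=60, wk 12 | n=60, wk 24 |
|---|---|---|---|---|---|
| 0.3 | 4 | 28 | 76 | 35 | 88 |
| 0.3 | 8 | 10 | 28 | 13 | 35 |
| 0.5 | 4 | 61 | 99 | 74 | 100 |
| 0.5 | 8 | 21 | 62 | 26 | 74 |
| 1.0 | 4 | >99 | 100 | >99 | 100 |
| 1.0 | 8 | 63 | >99 | 74 | >99 |

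Hand check of the lowest cell: the expected t is 0.83/(8/√45) = 0.83/1.19 ≈ 0.7, which fits a rejection rate near 10%.

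**The same simulation between arms.** The mean difference was within 0.05 month of zero. False positives were 4.3% to 5.9% for change and 4.4% to 5.4% for visit values. The SD of visit values was about 11 to 16 months, against about 4 to 8 months for change, so the age spread largely drops out of change scores.

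**After the fix.** With social age/chronological age × 100, the within-arm test is significant in about 4% to 6% of trials. The between-arm error rate stays near 5%.

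**The case against.** A reader might infer that ageing is mixed into the estimated treatment effect. The documents do not support that. The arms are randomised, concurrent and seen on the same schedule, so ordinary development is the same in both and cancels in the contrast. One qualification is last-observation-carried-forward imputation: with unequal dropout it would carry younger, lower social ages forward in one arm. That is a missing-data matter, and the article gives no reason to expect unequal dropout.

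It can also be said that the article never states that uncorrected social age is the analysed variable, and that the full protocol or SAP may name another score. This stands. The accurate statement is that no correction is stated, not that none exists. Even so, the article goes past the total score to social age and stops there, and it sets the tests for all continuous data explicitly.

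Third, the precision loss arises only if visit values are compared. The article does not say this for SMS, and its one defined outcome contrast, in the sample size section, is a change in CARS. This also stands and limits the point.

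Fourth, the paired tests are labelled secondary and nothing calls them evidence of efficacy. That is true, but a test that ordinary development alone can make significant is still better not reported as a test.

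**Conclusion.** The point holds in a limited form. As described, the within-arm SMS tests pick up ordinary development and cannot be read as gains in relative social maturity. The between-arm comparison is unbiased, but it forgoes precision that baseline SMS and age would give, mainly if visit values are compared.

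The sizes are 9% to 61% of visit-value variance from age, and within-arm rejection without any effect of 10% to over 99% at week 12 and 28% to 100% at week 24. All rest on assumed developmental rates, SDs and a uniform age distribution. It would go too far to say that a significant week-24 gain is nearly certain, because the slow-development, high-error scenarios give only 28% to 35%. What does not depend on the inputs tried is that every scenario exceeds the nominal 5%.

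The reach is one secondary outcome. The CARS analysis and the sample size do not change.

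**What to change.** State which SMS score is analysed. Then do one of the following:

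- Pre-specify the between-arm SMS comparison as ANCOVA with baseline SMS and exact age as covariates, used regardless of any baseline significance test. Baseline SMS already carries much of the age spread, and adding age costs nothing.
- Analyse social age divided by chronological age at that visit (× 100).

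In either case, report within-arm change in raw social age as descriptive only, without a significance test.

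The cost is one or two sentences in the analysis section and, for the second option, one derived variable. It needs only date of birth and visit dates, which a trial that selects on age and schedules its visits should hold. The one drawback is that within-arm SMS gains will look smaller.

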#### Child Health Questionnaire-Parent Report Form 28 (CHQ-PF28)

CHQ-PF28 has been used around the world as a tool to measure the general quality of life for children who are 5 or older. It has a verified internal consistency of 0.72 and a test-retest reliability of 0.31–0.84 [29]. The item scores are aggregated according to the calculation method set by HealthActCHQ, Inc. (Boston, MA, USA), and the higher score is interpreted as the higher quality of life. The assessment will be carried out during the visit of baseline (visit 2), mid-point (visit 14), termination (visit 25), and follow-up (visit 26).

#### EuroQoL Five-dimension Five-level Youth (EQ-5D-Y) proxy 1

EQ-5D-Y was transformed from EQ-5D to assess the quality of life of children and teens, and the proxy version is recommended for ages 4 to 7. The results of the multinational studies show that EQ-5D-Y has a test-retest reliability of 69.8–99.7%, Kappa coefficient of 0.67, and correlation coefficient of −0.56 with other tools [30]. Lower scores indicate better quality of life. The assessment will be carried out during the visit at baseline (visit 2), mid-point (visit 14), termination (visit 25), and follow-up (visit 26).

#### Korean Parenting Stress Index Short Form

Korean Parenting Stress Index Short Form (K-PSI-SF) was designed to measure the relative magnitude of stress that is experienced by parents in parent–child relationships. It is standardized for use on parents of children between the ages of 1 month and 12 years. For the US version of PSI, the internal consistency values were 0.70–0.83 in the children’s section, 0.70–0.84 in the parents’ section, and higher than 0.9 in the total stress score; the test-retest reliability values were 0.63 in the children’s section, 0.91 in the parents’ section, and 0.96 in the total stress score. For the Korean version of PSI, the Cronbach’s internal consistency was 0.76–0.91 and the test-retest reliability was 0.69–0.77 [31]. Scores of 15–80 percentiles are interpreted as normal range, 81–84 percentiles are boundary levels, and above 85 percentiles are risk levels. The assessment will be carried out during the visit at baseline (visit 2), mid-point (visit 14), termination (visit 25), and follow-up (visit 26).

### Safety assessment

To evaluate the safety of UGSJB, electrocardiogram and laboratory examinations (blood routine test, urine routine test, liver and kidney function test, and electrolytes) will be conducted on all participants at the screening phase (week 0) and post-treatment phase (week 12). At each visit, voluntarily reporting subjective or objective adverse symptoms will be collected to assess overall clinical safety by asking the question “Has there been any abnormal reactions since the last visit?” If participants drop out of our trial for treating any AEs, the AEs will be considered severe.

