## Background

Autism spectrum disorder (ASD) is characterized by continuous impairment in communication and social interaction (diagnostic criteria A) and by limited and repetitive behaviors, interests, or activities (diagnostic criteria B). These symptoms appear early in childhood and negatively affect daily functions (diagnostic criteria C and D) according to the *Diagnostic and Statistical Manual of Mental Disorders* (5th edition) [1]. The prevalence rate of ASD is four times higher for boys than for girls and has increased since the 1970s, especially from the late 1990s [2]. The prevalences of ASD are 2–20 per 1000 people in recent studies in Europe, Asia, and the US and 7.6 per 1000 people according to a global systematic review in 2010 [3]. Causes of ASD are unclear, but gene abnormalities altering brain development, brain damage at birth, and maternal effects during pregnancy have been suggested.

General therapeutic goals of ASD are to reduce behavioral disabilities, improve verbal/non-verbal communication, and provide patients with self-reliance skills. Non-pharmaceutical treatments aim to improve ASD symptoms through individualized behavioral and educational interventions, including behavioral and developmental programs, cognitive behavioral therapies, occupational therapies, sensory integration therapies, sleep management, and communication facilitation [4]. Pharmaceutical treatments, including risperidone, aripiprazole, methylphenidate, and haloperidol, are generally used as adjunctive therapies to reduce the accompanying symptoms such as aggression, anxiety, depression, hyperactivity, stereotypic and self-harm behavior, and insomnia rather than the core symptoms of ASD [5]. However, there has been a lack of systematic verification and consensus regarding the treatment of the core symptoms of ASD because of its unclear etiology.

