Ukgansangajinpibanha (UGSJB), which is made from Ukgansan by adding Citri Pericarpium and Pinelliae Rhizoma, has been more often used in children with indigestion compared with Ukgansan. Similar to Ukgansan, it has been administered to angry, sensitive, nervous, and unsettled children with ASD [13]. Unlike Ukgansan, UGSJB is legitimately prescribed as an herbal formula granule for nervousness, insomnia, night crying, and malnutrition in South Korea and Japan [14]. Interestingly, children with ASD tend to experience more gastrointestinal symptoms than children without ASD [15]. Therefore, we prepared a well-designed clinical trial to investigate the safety and effectiveness of UGSJB on ASD symptoms compared with placebo treatment. The results of this trial will provide evidence of whether UGSJB is safe and effective for the treatment of ASD in children.

Acupuncture, a treatment supported by the National Health Service in South Korea, will be provided to every participant for an economic evaluation. Acupuncture has weak evidence of benefits but is a safe and effective treatment for ASD [16]. Frequently used acupoint for treating ASD sympstoms are EX-HN1, GV17, PC6, LR3, KI3, HT7, LU9, GV20, GV24, GV24.5, GB13, GB19, KI4, LR4, ST36, SP3, and SP6 [17]. We decided to use EX-HN1, GV20, and GV24 for acupuncture treatment of ASD in children because these acupoints have been frequently used in RCTs on ASD [18], and scalp acupuncture decreased scores of Childhood Autism Rating Scale (CARS) and Autism Behavior Checklist (ABC^1^) of children with ASD [19]. UGSJB in combination with acupuncture will be evaluated from an economic perspective.

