After screening, suitable participants will be randomly assigned to the 3.0 g/day UGSJB or placebo group. UGSJB granule is composed of nine herbs: Ban Xia (*Pinellia ternate*), Bai Zhu (*Atractylodes japonica*), Fu Ling (*Poria cocos*), Dang Gui (*Angelica gigas*), Chen Pi (*Citrus unshiu*), Chuan Xiong (*Cnidium officinale*), Diao Gou Teng (*Uncaria sinensis*), Chai Hu (*Bupleurum falcatum*), and Gan Cao (*Glycyrrhiza glabra*) (Table 1). Placebo granule is composed of 0.95 g lactose, 0.4 g corn starch, and 0.15 g caramel pigment to match the UGSJB. UGSJB and placebo granules were manufactured and stored by Kyungjin Pharmaceutical Co., Ltd. (Gyeonggi, Republic of Korea). The solvent used in the extract was purified water, and the ratio of extract to herbal drugs was about 12.2%. Storage, dispensation, and quality control of the UGSJB and placebo granules were carried out by a blinded pharmacist in each study center. Caregivers will be instructed to dissolve in water and administer one pack (1.5 g) of UGSJB or placebo granule after breakfast and dinner for 12 weeks, which was the period that reported effectiveness in previous studies [11, 12]. The dosage regimen was determined by referring to the authorization by the Ministry of Food and Drug Safety and the clinical judgment of Korean medicine doctors. The quantities of marker constituents per pack were 3.99 mg of glycyrrhizinate and 11.18 mg of hesperidin. Lead and microorganisms were not detected, and the concentration of arsenic was 0.33 parts per million in one pack of UGSJB. The UGSJB or placebo will be prescribed by Korean medicine doctors with more than 5 years of clinical experience. If there are any adverse events (AEs) related to UGSJB, such as pseudoaldosteronism, myopathy, allergic skin reaction, and gastrointestinal upset, that participant will stop taking medication and will receive appropriate treatment according to the severity of the AEs. The guardians should return the used as well as unopened packages to check the adherence to treatment.

**Table 1 Tab1:** Composition of Ukgansangajinpibanha granule

Plant name	Used part	Registration	Amount, grams
*Pinellia ternate* Breitenbach (Araceae)	Dried rhizome	KP	0.84
*Atractylodes japonica* Koidz. (Compositae)	Dried rhizome	KP	0.67
*Poria cocos* Wolf (Polyporaceae)	Dried scleorotia	KP	0.67
*Angelica gigas* Nakai (Umbelliferae)	Dried root	KP	0.5
*Citrus unshiu* Markovich (Rutaceae; citrus peel)	Dried fruit peel	KP	0.5

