## Discussion

Herbal medicines which have been shown to be effective for ASD in RCTs include Jiawei Wendan decoction, modified Yinhuo decoction, and supplemented Lizhong decoction [34]. Modified Yinhuo decoction and supplemented Lizhong decoction improve CARS and the total effective rate, and Jiawei Wendan decoction improves the total effective rate. However, there were some methodological limitations. For example, the number of participants in each group was less than 30 and all studies were unblinded. Our study will be the first prospective, multicenter, randomized, double-blinded, placebo-controlled, parallel-group clinical trial assessing the safety, effectiveness, and economics of an herbal medicine combined to acupuncture in the treatment of ASD.

ASD is generally diagnosed around 4 years of age [35], and the UGSJB dose administered to 4- to 6-year-old children ages is half that of adults. Moreover, the golden time for ASD treatment is known to be between the ages of 2 and 6 [36]. We decided to enroll 4- to 6-year-old children with ASD for the best effectiveness using a single capacity of UGSJB. The treatment period was set to be 3 months, following the previously effective herbal treatment RCTs. Acupuncture, a treatment supported by the National Health Service in South Korea, will be implemented in all groups for economic comparison. The behavior of children with ASD will be evaluated by CARS, ABC^1^, and ABC^2^. Social maturity will be assessed by SMS. Quality of life will be evaluated by CHQ-PF28 and EQ-5D-Y proxy 1. Stress of parents of children with ASD will be assessed by K-PSI-SF. The safety of USGJB will be investigated on the basis of voluntarily reported AEs, and the economic evaluation of USGJB will be analyzed by CEA, CUA, and CBA.

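### Symptomatic adverse events rest on one open, unprompted question with no named respondent, so the four reactions the protocol itself lists may be under-recorded in both arms

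*Protocol article*

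**What the plan says.** The Safety assessment section sets out two sources of harm data.

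- **Symptoms.** The section states that "voluntarily reporting subjective or objective adverse symptoms will be collected to assess overall clinical safety by asking the question". The enquiry is put at every visit and is worded in general terms: "Has there been any abnormal reactions since the last visit". The section does not say whether the child or the guardian answers.
- **Tests.** In the same section, "electrocardiogram and laboratory examinations (blood routine test, urine routine test, liver and kidney function test, and electrolytes) will be conducted on all participants", at screening (week 0) and after treatment (week 12).

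The Discussion sums up the safety basis by the first source only: safety "will be investigated on the basis of voluntarily reported AEs".

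The Interventions section names the reactions of interest, adverse events "related to UGSJB, such as pseudoaldosteronism, myopathy, allergic skin reaction, and gastrointestinal upset", and ties an action on study medication to them. The Background says that autism spectrum disorder "is characterized by continuous impairment in communication and social interaction", and that "children with ASD tend to experience more gastrointestinal symptoms than children without ASD". Eligible children are 4 to 6 years old with a CARS score of at least 30.

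**The concern.** The protocol knows which reactions it is looking for, but its symptom question asks about none of them. An open question records what the respondent notices, thinks worth mentioning and connects with the study. A rash can be seen. Muscle pain, weakness and abdominal discomfort are largely felt, so the person answering depends on what the child shows or conveys, and impaired communication is part of the diagnosis.

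Safety is the first word of the trial's title. If symptomatic reactions are recorded incompletely, a short adverse event list could be read as reassurance when it partly reflects how the question was put. Symptoms not asked about during treatment cannot be recovered at analysis.

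**Working it through.** **1. The protocol's own figures.** The article states no figure for detecting adverse events. The only usable input is the number per arm. The Sample size calculation section gives CARS changes of −7.9 (SD 5.42) and −4.6 (SD 5.53), a difference of 3.3.

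- Pooled SD = √[(5.42² + 5.53²)/2] = 5.475.
- A two-sample t test at two-sided 5% and 80% power needs 44.2, so 45 per group, as stated.
- Allowing for 25% withdrawal, 45/0.75 = 60 per group, as stated.

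I use 60 per arm. The Abstract shows 120 per group, but Study participants and Sample size calculation both give 120 in total.

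**2. Coverage of the four named reactions.**

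| Reaction named in Interventions | Named in the visit question? | Test listed in Safety assessment |
|---|---|---|
| Pseudoaldosteronism | No | Electrolytes and ECG, weeks 0 and 12 |
| Myopathy | No | No muscle-specific test; electrolytes bear on it indirectly, since Interventions links myopathy to pseudoaldosteronism or hypokalaemia |
| Allergic skin reaction | No | None stated |
| Gastrointestinal upset | No | None stated |

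With tests at two time points, a change that arises and resolves between them can be missed.

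**3. How often the question is put.** There are 24 treatment visits, two a week, and one follow-up visit 12 weeks after the last treatment. Recall gaps are short during treatment and long only at follow-up. The weakness is the missing prompt, not recall.

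**4. What incomplete capture does.** Let p be the true risk in an arm and c the share of true cases that the open question records. Assume c is the same in both arms.

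- Recorded risk = c·p, and expected recorded cases = 60·p·c.
- P(at least one recorded) = 1 − (1 − p·c)^60.
- Recorded risk difference = c·(p₁ − p₂), which shrinks by the factor c.
- Recorded risk ratio = (c·p₁)/(c·p₂) = p₁/p₂, which is unchanged.

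**5. Illustration.** Neither p nor c is in the article, so all values below are assumptions.

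| True risk | Capture | Expected recorded cases in 60 | P(at least one recorded) |
|---|---|---|---|
| 10% | 100% | 6.0 | 0.998 |
| 10% | 50% | 3.0 | 0.954 |
| 10% | 25% | 1.5 | 0.781 |
| 5% | 100% | 3.0 | 0.954 |
| 5% | 50% | 1.5 | 0.781 |
| 5% | 25% | 0.75 | 0.530 |
| 2% | 100% | 1.2 | 0.702 |
| 2% | 50% | 0.6 | 0.453 |
| 2% | 25% | 0.3 | 0.260 |

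For a comparison of proportions, power = Φ[(d − 1.96·SE₀)/SE₁], with SE₀ from the pooled proportion and SE₁ from the separate ones. Take true risks of 20% and 5%:

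- c = 1: d = 0.150, SE₀ = 0.0604, SE₁ = 0.0588, power 0.70.
- c = 0.75: d = 0.1125, SE₀ = 0.0532, SE₁ = 0.0522, power 0.56.
- c = 0.5: d = 0.075, SE₀ = 0.0442, SE₁ = 0.0437, power 0.40.

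The ratio stays at 4 throughout. These figures show direction and range, not an estimate for this trial.

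**The case against.** The strongest reply has five parts.

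- **Safety does not rest on the question alone.** This stands. A reader might infer so from the Discussion, but Safety assessment plans ECG, electrolytes and other laboratory tests for everyone. The point is limited to symptomatic events.
- **The guardian is probably the one who answers.** Caregivers give the medication, guardians return the packs and receive visit reminders, and quality of life is collected by parent or proxy forms. This is likely, and it weakens the communication argument. It does not remove it for felt symptoms, and the text should name the respondent.
- **The arms are treated alike.** Both get the same question under double blinding. A reader might infer a distorted comparison between arms. With equal capture the risk ratio is preserved; only absolute rates, the absolute difference and power suffer.
- **Pre-existing gut complaints.** A reader might infer that these cannot be told from new ones and would end medication in either arm. The article does not support that. The question asks about change since the last visit, it is put at each visit, visit 2 is labelled baseline for the secondary outcomes, and the action in Interventions is confined to events judged related to the granule.
- **A checklist may sit in the full protocol or case report form.** It may, and for that reason the finding is confined to this text. But the article does more than stay silent: it quotes the question and twice describes reporting as voluntary, which would fit badly with a prompted checklist.

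**Conclusion.** The point holds for symptomatic adverse events. Their collection is fixed as voluntary report to one open question, with no stated respondent and no prompt for the reactions the protocol lists. Skin and gut reactions have no stated objective check, and no muscle-specific test is listed. Under-counting in both arms is a reasonable risk, greatest for felt symptoms. It would lower recorded rates and the power to see a difference.

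A reader might go further and conclude that harms will be under-counted by some stated amount. The documents cannot support that: they give neither event rates nor a capture rate, and asking twice a week during treatment works in the other direction. The figures above rest on assumed risks, assumed capture equal in both arms, and 60 children per arm. The change is worth making because it is cheap now and impossible after the data are collected.

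**What to change.** 1. Keep the open question and ask it first, so that volunteered events remain comparable with other trials.
2. Name the guardian as respondent.
3. Then ask four fixed yes/no items in lay words, one for each reaction already named in Interventions, at visit 2 before the first pack and at every later visit to visit 26.
4. Classify a prompted item as treatment-emergent only if it is new or worse than at visit 2.
5. Report prompted and volunteered events separately by arm.
6. Amend the references to voluntary reporting in Safety assessment and in the Discussion, and mention the ECG and laboratory tests in the Discussion's summary of safety.

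The relatedness judgement and the action on study medication in Interventions stay as they are.

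The cost is four tick boxes at visits already held. The drawback is that more minor events will be recorded in both arms, which is the reason for reporting the two sources separately.
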